#### Adaptive design modification criteria

The mean scores of the main outcomes (side hop and ACL-RSI) will be compared in exploratory interim analyses once *n*=25 participants have been included in both groups. Analyses will be performed by a blinded third-party data management committee (DMC) and blinded to treatment arms until after an initial data analysis and interpretation. The purpose of the interim analysis is primarily to gain data with which a more reliable sample size can be calculated based on observed differences, as well as to identify potential benefits and harms which may thereby determine whether modifications are required. Therefore, differences in the main outcomes from baseline to 12 weeks will be compared using estimations from the previously defined clinically relevant differences as modification criteria, as both groups are expected to improve. Continuation without modification will be allowed if the between-groups difference in ACL-RSI is ≥5 points, and/or muscle function (LSI) in the side-hop test is ≥8 in favor of the MOTIFS group, each analyzed separately. These estimates correspond to a small to medium effect size (Cohen’s *d*≈0.1–0.3) based on previously defined clinically relevant values and will be used to determine the potential for the MOTIFS model to exhibit an effect. However, as previous studies which provide enough data for reliable calculation are lacking, these effect sizes are theoretical estimations which require further data to confirm. The estimates take into account the small sample size in the interim analysis and serve as a guide to whether the differences exhibit a trend indicating acceptable power upon completion of data collection, without unnecessarily prematurely ending the trial. If these initial criteria are not met, difference in enjoyment (PACES) scores of approximately 5 points will be deemed acceptable, estimated based on studies examining the effect of enjoyment on physical activity adherence in uninjured people [53]. Increased adherence to rehabilitation training will likely lead to improved rehabilitation outcomes based on a dose-response relationship, so increased enjoyment is considered an acceptable criterion for the continuation of the trial. Upon completing the interim analysis, the DMC will determine whether these criteria are met, and/or whether modifications are necessary, and a new sample size calculation will be performed.

Modification recommendations will be made based on observed data to identify potential harms or an unrealistic new estimated sample size estimation (i.e., more than 100 patients in each group), for example. In this case, the method will be refined to ensure that the model’s efficacy is maximized according to the proposed outcomes (i.e., psychological readiness to return to sport and muscle function results) and that implementation is clinically relevant and feasible for the end-users. Pilot testing will then be performed again, examining a new pilot population a maximum of one additional time to evaluate whether a satisfactory level of clinically relevant power is achieved (i.e., continuation criteria are met), thereby justifying the continuation of the trial. Modifications will be informed by preliminary results from interim analyses of this cumulative adaptive trial examining both participant data and PT interview responses in the research team, DMC, and potentially discussions with a focus group comprised of end-users (PTs and patients). Following the initial interim analysis, the *p* value will be adjusted using a Bonferroni correction to take into account the risk of type-I error inherent in repeating the pilot phase.

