### Statistical analyses

#### Sample size

Based on previous studies examining ACL-RSI [49] and side-hop function [50], a preliminary sample size was estimated, to be used in the first phase of this adaptive RCT, which resulted in *n*=106 participants. This included adjustments for potential cluster effects using a preliminary Intra-Cluster Correlation Coefficient (ICC). An approximation is required as comparable studies are unavailable to reliably perform a sample size estimation. This is necessary in this phase in order to evaluate whether an intervention effect is detectable and within practical limitations, which will thereafter inform more accurate sample-size estimations.

A new sample size will be calculated by a blinded third-party member of the data management committee using collected data from an interim analysis, therefore allowing for more accurate between-group differences in the main outcomes. Observed within- and between-cluster variance will also be calculated in order to more accurately estimate an Intra-Cluster Correlation Coefficient (ICC, denoted as *ρ*). This will be performed using the formula $$ \rho =\frac{s_b^2}{s_b^2+{s}_w^2} $$ [51] in order to adjust for the fact that different clinics are included in the trial (i.e., potential clustering effects). The adjusted sample size will therefore be calculated using the formula $$ \frac{n_ik\left(1-\rho \right)}{k-{n}_i\rho } $$ [52], along with an estimated 20% drop-out rate, in order to reach a power of 0.80, with significance set at *p*<0.025. As an estimated sample size has been calculated, the new sample size will only be adjusted up; that is, the number of participants included will not be less than *n*=106 required in the original sample-size estimation.

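### On the plan's own effect sizes, an interim ACL-RSI result at the continuation threshold also trips the 100-per-group modification trigger, and meeting that threshold does not indicate acceptable power

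*Protocol article*

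**What the plan says.** All statements are in the protocol article, under Statistical analyses.

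- **Continuation rule** (Adaptive design modification criteria): "Continuation without modification will be allowed if the between-groups difference in ACL-RSI is ≥5 points". A second route, through the side hop, is attached to this one: "and/or muscle function (LSI) in the side-hop test is ≥8 in favor of the MOTIFS group, each analyzed separately".
- **Effect size of the thresholds** (same section): "These estimates correspond to a small to medium effect size (Cohen’s *d*≈0.1–0.3"). The section adds that these effect sizes are theoretical and need data to confirm them.
- **Meaning of the thresholds** (same section): they "serve as a guide to whether the differences exhibit a trend indicating acceptable power upon completion of data collection". On a possible repeat pilot, the section describes the question as "whether a satisfactory level of clinically relevant power is achieved (i.e., continuation criteria are met").
- **Modification trigger** (same section): one reason to recommend modification is "an unrealistic new estimated sample size estimation (i.e., more than 100 patients in each group), for example". The text then says that the method is to be refined and a new pilot population examined, at most once more.
- **Re-estimation** (Sample size): the new size uses interim data, a cluster adjustment and 20% drop-out, "in order to reach a power of 0.80, with significance set at" p<0.025. It can only go up from 106.

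On completing the interim, the data management committee decides whether the criteria are met and/or whether modification is needed. The section does not say which rule prevails when they disagree.

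**The concern.** Both rules act on the same interim data, from 25 participants per group. The first lets the trial go on unmodified at an effect that the plan itself calls small to medium. The second treats the trial as unrealistic if the effect found needs more than 100 per group. Small to medium effects usually need more than that at 80% power, so the same result could meet both rules.

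The choice between them decides whether the intervention is changed, whether a new pilot population is recruited, and whether the p value is Bonferroni-adjusted for repeating the pilot. If the plan does not settle it, it will be settled after the data are seen. In addition, a committee that takes the thresholds as evidence of adequate power would be misinformed.

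**Working it through.** **Inputs.** Thresholds of 5 ACL-RSI points and 8 LSI points, d≈0.1–0.3, limit of 100 per group, and interim at 25 in both groups (read as 25 per group): Adaptive design modification criteria. Power 0.80, p<0.025, drop-out 20%, floor of 106: Sample size. Allocation 1:1: Study design. Sidedness is not stated. Two-sided is used, and the most lenient alternative is shown.

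**The plan's own figure.** The total of 106 cannot be reproduced, because the article does not give the effect size, SD, ICC or number of clusters behind it. Nothing below depends on reproducing it.

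**Step 1: size needed at the plan's d.** Normal approximation, per arm: n = 2(z₁₋α/₂ + z₀.₈₀)²/d². Here 2(2.2414 + 0.8416)² = 19.01.

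| d | n evaluable per arm | enrolled per arm, n/0.80 |
|---|---|---|
| 0.3 | 19.01/0.09 → 212 | 265 |
| 0.2 | 19.01/0.04 → 476 | 595 |
| 0.1 | 19.01/0.01 → 1902 | 2378 |

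The most lenient variant is one-sided 0.05 with no drop-out and no clustering. At d=0.3 it gives 2(1.6449 + 0.8416)²/0.09 → 138 per arm. Every variant exceeds 100, and a cluster adjustment that enlarges the sample widens the gap.

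**Step 2: where the two rules stop overlapping.** Solve 19.01/d² = n for d.

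- Limit read as 100 evaluable per group: d = √(19.01/100) = 0.44.
- Limit read as 100 enrolled, so 80 evaluable: d = √(19.01/80) = 0.49.

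An ACL-RSI result from the threshold (d≈0.1–0.3) up to 0.44–0.49 meets both rules. Larger effects meet the continuation rule without tripping the trigger.

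**Step 3: dependence on the SD.** The rule is written in points, so the overlap depends on the SD of ACL-RSI change.

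- SD implied by the plan's mapping: 5/0.3 = 16.7 to 5/0.1 = 50.
- SD at which a 5-point difference needs exactly 100 per group: 5/0.436 = 11.5 without drop-out, 5/0.487 = 10.3 with 20% drop-out.
- In points, with SD 16.7: the overlap runs from 5 to 0.436×16.7 = 7.3 points (no drop-out) or 0.487×16.7 = 8.1 points (20% drop-out).

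**Step 4: power at the threshold.** Power ≈ Φ(d√(n/2) − 2.2414), n per arm, d=0.3, before clustering.

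| Evaluable per arm | Calculation | Power |
|---|---|---|
| 53 (106 in total) | Φ(1.544 − 2.241) | 0.24 |
| 42.4 (106 less 20%) | Φ(1.381 − 2.241) | 0.195 |
| 100 | Φ(2.121 − 2.241) | 0.45 |

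At d=0.1 the power is 0.04 with 53 per arm and 0.06 with 100 per arm.

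**Step 5: the side-hop threshold.** It is set on LSI. Under Main outcomes, the side-hop main outcome is change in the number of hops in the injured leg, and re-estimation uses the main outcomes. An effect size for LSI does not give the sample size for hops, so steps 1 to 3 apply directly only to ACL-RSI.

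**The case against.** The strongest reply is that the rules are meant as two stages: a first screen on the thresholds, then a feasibility check on the re-estimated size, with the committee using judgement. The wording gives some support. Continuation is something the plan allows, modification is framed as a recommendation, and the limit of 100 is introduced as an example. A reader might infer that the plan orders both continuation and modification. That goes too far. What stands is that the text then says the method is to be refined, and it gives neither rule priority.

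A reader might also infer that the plan promises 80% power with 106 participants for these differences. It does not. The 0.80 belongs to the re-estimated size, 106 is a preliminary floor, and the limitations in the Discussion call the means and SDs theoretical. The power at 106 in the working shows only what the thresholds would mean at that size.

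Third, the d range is provisional, so the overlap is conditional and a small enough observed SD would remove it. That is correct. Still, it is the only mapping the plan gives, and its implied SD of 16.7 or more lies well above the 10 to 11 points required.

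Finally, calling the thresholds a guide to a trend is a modest claim. The later phrase that explains satisfactory power as the criteria being met is not.

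**Conclusion.** The point holds as an internal inconsistency, in two parts.

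1. **Conflicting rules.** On the plan's own mapping, an ACL-RSI difference at the continuation threshold implies at least 212 evaluable per arm, more than twice the 100 called unrealistic. Results up to d of about 0.44 to 0.49 meet both rules, without stated precedence.
2. **Power statement.** Meeting the thresholds does not indicate acceptable power. At the top of the stated range, power is about 24% with 106 evaluable and 45% with 100 evaluable per group, both before clustering.

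This assumes two-sided testing at 0.025, re-estimation on the observed difference, and an SD of ACL-RSI change above about 10 to 11 points. The conflict at d=0.3 survives one-sided testing at 0.05 without drop-out. It should not be extended to the LSI threshold by the same arithmetic, nor read as a flaw in the final test.

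**What to change.** Before the interim analysis, amend the sample size and adaptive design text so that it gives one rule:

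- Keep the 5-point and 8-point thresholds only as a sign of a favourable direction and no harm.
- Delete both statements that meeting them indicates acceptable or satisfactory power.
- State that the re-estimated size, set against the 100-per-group limit, takes precedence when the two disagree, or reconcile the passages into a single rule in another way.
- Base the side-hop criterion on the measure used for re-estimation, change in hops in the injured leg.

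**Cost.** This is a wording change. The article reports 35 participants included, short of 25 per group, so at that point there was time to make it. No extra patients are needed. The stated meaning of the continuation criteria becomes less favourable.

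Precedence for the re-estimated size also has a price that the team should accept knowingly. With 25 per arm the standard error of d is √(2/25) = 0.28. If the true d were 0.6, the observed d would fall below 0.49 with probability Φ((0.49 − 0.6)/0.28) ≈ 0.35. That sits uneasily with the plan's wish not to end the trial too early, which is why another single rule would also be acceptable.

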**Methods:**

This pragmatic 1:1 single assessor-blinded adaptive cumulative cluster-randomized controlled trial will include 106 knee-injured people with a goal of returning to physical activity. Participants are randomized to either the MOTIFS or Care-as-Usual condition. Primary outcomes are the ACL Return to Sport after Injury Scale and change in injured leg hop performance in a side hop task from baseline to 12 weeks. Secondary outcomes include patient-reported outcomes and assessment of muscle function using a hop test battery and Postural Orientation Errors at 12-week follow-up. At 12-month follow-up, patient-reported outcomes are assessed. A sub-group (7-10 in each group) will be interviewed to gain insight into experiences of rehabilitation.

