#### Outcome assessment

Physical and patient-reported outcomes are assessed at baseline and 12 weeks; patient-reported outcomes are assessed 12 months post-inclusion (Fig. 1). Prior to the testing occasion, self-report questionnaires are distributed using the REDCap electronic data capture tool [32], hosted by Lund University. Demographic data (age, gender, height, weight, treatment type, and injury history) and physical testing data (Table 3) are collected by an experienced test-leader either at the participants’ respective clinics or at the university lab according to a data collection form including testing procedures (further information is available in the data management plan, available at the ClinicalTrials.gov registration page: NCT03473821). Outcomes are assessed at 12 weeks post-inclusion to assess physical and psychological readiness when a PT would likely consider a return to activity testing, and at 12 months to assess long-term rehabilitation outcomes.

**Table 3 Tab3:** Outcomes assessment—description of types of outcome and the data used for analysis

Outcome		Type	Outcome data
Patient-reported outcomes	ACL-RSI^a^	12 item self-report scale (0–100 for each item)	0% (worst) to 100% (best) mean of summed total score
	KOOS	The normalized score for subscales: pain, symptoms, sports and recreational activity, activities of daily life, and quality of life	0 (worst) to 100 (best)
	PACES	18-item self-report scale (11 items reverse-scored)	18 (worst)–126 (best)
	PSS	10-item self-report scale	0 (best) to 40 (worst); 0–13 = low, 14–26 = moderate, 27–40 = high stress
	PEI	6-item self-report	0 (worst) to 12 (best)
	ROS	1-item self-report scale	Satisfied (3 or 2), mostly satisfied (1), or dissatisfied (0, −1, −2, or −3)
	RM	3-item self-report scale	0 (worst) to 10 (best); raw data presented
	TAS	3-item self-report scale (pre-injury, current, future)	1 (low activity)–10 (very high activity)
Physical testing	SH^a^	Number of completed hops	Change in the injured leg
	Hop test battery	SLHD-3 repetitions or until improvement <10cm; distance hopped (cm)	Change in the injured leg, change in the uninjured leg, LSI
		SH-number completed hops in 30 s	
	POEs	SLMS-5 repetitions; POEs assessed throughout the entire movement	Total POEs score
		SD-5 repetitions; POEs assessed on loading leg throughout entire movement until both feet are on the floor	
		FL-3 repetitions; POEs assessed on the front leg from landing until maximum flexion of the knee	

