#### Main outcomes

This trial includes two main outcomes. Psychological readiness to return to sport is evaluated using the Swedish version of the ACL-Return to Sport after Injury scale (ACL-RSI), which includes an emotional response, confidence, and risk-appraisal when returning to sport after an ACL injury [33, 34]. Physical function is evaluated using the change in number of hops in the injured leg from baseline to 12 weeks for the side hop task.

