##### Hop test battery

The hop test battery [6], consisting of two functional tasks (single-leg hop for distance and side hop) performed on both legs, is used to evaluate muscle function. The single-leg hop for distance is done by standing on one leg and performing a maximal jump forward, landing with control on the same leg, and maintaining control for 2–3 s. Failure to maintain landing position results in a disqualified hop and the hop will be repeated. The side hop task is performed by jumping on one leg from side to side over two parallel lines taped 40 cm apart on the floor as many times as possible in 30 s [44]. The number of successful hops without touching the line is recorded. Results are expressed as change in the injured leg, change in the uninjured leg, and limb symmetry index (LSI; LSI = (injured leg/uninjured leg) x100) individually and summed.

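### The interim side-hop criterion is set on Limb Symmetry Index, not on the injured-leg hop count that is the main outcome

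*Protocol article*

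**What the plan says.** **Main outcome.** The abstract (Methods) names "change in injured leg hop performance in a side hop task from baseline to 12 weeks" as the physical primary outcome. The Main outcomes section repeats it as "the change in number of hops in the injured leg from baseline to 12 weeks for the side hop task". In Table 3 the side-hop row that carries the main-outcome mark is the completed-hop count, analysed as change on the injured leg.

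**LSI.** In Table 3 it appears only in the hop test battery row, as one of three results: "Change in the injured leg, change in the uninjured leg, LSI". The Hop test battery section, which falls under secondary outcomes, defines it: "LSI = (injured leg/uninjured leg) x100".

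**Interim.** The section on adaptive design modification criteria opens with "The mean scores of the main outcomes (side hop and ACL-RSI) will be compared in exploratory interim analyses". The side-hop threshold that follows is "muscle function (LSI) in the side-hop test is ≥8 in favor of the MOTIFS group, each analyzed separately". It is linked by and/or to an ACL-RSI difference of at least 5 points. If neither is met, a fallback applies: "difference in enjoyment (PACES) scores of approximately 5 points will be deemed acceptable". No criterion is given in injured-leg hops, and no reason is given for using LSI.

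**Re-estimation.** The Sample size section says the new sample size uses interim between-group differences in the main outcomes.

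**The concern.** The section announces a comparison of main outcomes and then applies its side-hop threshold to a secondary one. The two are not interchangeable. LSI is a ratio with the uninjured leg in the denominator, so it changes when that leg changes, whatever the injured leg does. The intervention is built into hop, change-of-direction and pivoting exercises, and the plan itself measures change in the uninjured leg, so movement in the denominator is a realistic possibility.

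What is at stake is the decision to continue or modify. The section presents its thresholds as a guide to whether power will be acceptable at the end of the trial, but a difference in LSI says little about power for injured-leg hops. As written, the continuation rule and the sample-size re-estimation also use different side-hop variables. A decision to modify is costly: it leads to a refined method, a second pilot population and a Bonferroni-adjusted significance level.

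**Working it through.** **The plan's own figure.** The only side-hop figure is the threshold of 8, given without a unit and read here as LSI percentage points. The section attaches d of about 0.1 to 0.3 to its thresholds. For the LSI threshold that implies an SD between 8/0.3 = 26.7 and 8/0.1 = 80 LSI points. Nothing in the article converts this to hops: it gives no hop difference and no SD of hop change.

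**Can the two variables disagree?** The formula is the article's: LSI = 100 × injured / uninjured. All hop counts below are assumed. The rule is a between-group difference, so both arms are needed. Both start at 30 injured and 40 uninjured, LSI = 100 × 30/40 = 75.0. With equal baselines, the difference in 12-week LSI equals the difference in change.

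*Case 1: criterion met, no difference in the main outcome.*
- MOTIFS: injured +8, uninjured 0. LSI = 100 × 38/40 = 95.0.
- Care-as-usual: injured +8, uninjured +4. LSI = 100 × 38/44 = 86.4.
- LSI difference = +8.6, which meets the criterion. Main-outcome difference = 8 − 8 = 0 hops.

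No leg gets worse in either arm, which fits the plan's expectation that both groups improve.

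*Case 2: criterion not met, MOTIFS better on the main outcome.*
- MOTIFS: injured +12, uninjured +12. LSI = 100 × 42/52 = 80.8.
- Care-as-usual: injured +6, uninjured 0. LSI = 100 × 36/40 = 90.0.
- LSI difference = −9.2. Main-outcome difference = 12 − 6 = 6 hops in favour of MOTIFS.

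**How often?** This is an illustrative simulation with 4,000 repetitions and 25 per group (the interim size read as per group). Assumptions: mean baselines 30 and 40; baseline SD 8 shared between legs plus 3 per leg; SD of change 6 hops; leg-to-leg correlation of change 0.6; mean care-as-usual gains of 8 injured and 2 uninjured; counts floored at 8; no clustering.

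| Extra MOTIFS gain, injured / uninjured | Mean hop difference, injured leg | Mean LSI difference | Chance of LSI ≥8 |
|---|---|---|---|
| 0 / 0 | 0.0 | 0.0 | 3% |
| +5 / 0 | 5.0 | 12.8 | 85% |
| +5 / +5 | 5.0 | 0.8 | 4% |
| 0 / −5 | 0.0 | 13.9 | 88% |

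The second and third rows have the same main-outcome effect, yet the chance of meeting the criterion is 85% in one and 4% in the other. The last row is a stress case, since the MOTIFS uninjured leg then loses 3 hops on average (2 − 5).

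**How the criteria combine.** Under and/or, meeting LSI alone is enough to continue unmodified. Failing LSI is not enough to miss the continuation criteria, because ACL-RSI or, after it, PACES can still satisfy the rule. The exposure is therefore mainly on the side of continuing when the injured leg shows nothing.

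**The case against.** The interim is labelled exploratory, its thresholds are described as a guide, and its primary purpose is sample-size re-estimation. There is no early stop for efficacy, the sample size can only go up, and the final analysis concentrates on the two main outcomes. The ACL-RSI criterion is on a main outcome. Injured-leg hops still reach the decision indirectly, because the re-estimated size depends on the main outcomes and an unrealistic size, for example more than 100 per group, can prompt modification. LSI also has a clinical rationale: the Background links limb asymmetry in hop performance to return to activity.

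Most of this stands as a limit on the consequences. It does not remove the inconsistency: the section says main outcomes and uses a secondary one, and nothing elsewhere in the article reconciles the two. The Background supports interest in LSI, but the article does not offer it as the reason for the interim choice.

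A reader might also infer that the PACES fallback could be met by greater enjoyment under care-as-usual, since its sentence names no arm. The same section goes on to justify the fallback by increased enjoyment leading to better adherence, and its stated aim is to judge the potential of MOTIFS. The direction is therefore implied, and only the wording needs tidying.

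**Conclusion.** The point holds as a mismatch between the interim side-hop criterion and the main outcome. The contradiction rests on the article's text alone. Its size depends on assumed hop counts, because the article supplies none: LSI can clear the threshold by 8.6 against 8 with a main-outcome difference of zero, and can read −9.2 when MOTIFS is 6 hops better. The simulated percentages illustrate how far the two can part and are not estimates for this trial.

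Three stronger conclusions are tempting and are not supported. The final test is not compromised, since it still uses the injured-leg change. Missing the LSI threshold does not by itself force modification. Nor is the interim decision cut off from the main outcomes altogether, given the ACL-RSI criterion and the re-estimation. What is affected is the continue-or-modify decision, chiefly the chance of continuing unmodified on LSI alone.

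**What to change.** Before the interim, restate the side-hop criterion as the between-group difference in change in injured-leg side-hop count, in favour of MOTIFS, using the same variable and SD as the sample-size re-estimation. The sponsor should set the threshold in hops and justify it. Give LSI to the data management committee as supportive information only. As a wording matter, name MOTIFS as the favoured arm in the PACES fallback.

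The injured-leg count is already collected, so no new data are needed. The real cost is the threshold: no hop difference or SD can be taken from the article, which itself says reliable prior data are lacking, so a new justification has to be written. If the sponsor prefers to keep LSI, it should say why and acknowledge that the criterion is not on the main outcome.

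Timing matters, because changing the rule after seeing interim data would undermine it. The Trial status section reports 35 participants included. If the interim is read as 25 per group (50 in total), it was still ahead at the time of writing.
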